## Abstract

Sleep-wake disturbances frequently present in Veterans with mild traumatic brain injury (mTBI). These TBI-related sleep impairments confer significant burden and commonly exacerbate other functional impairments. Therapies to improve sleep following mTBI are limited and studies in Veterans are even more scarce. In our previous pilot work, morning bright light therapy (MBLT) was found to be a feasible behavioral sleep intervention in Veterans with a history of mTBI; however, this was single-arm, open-label, and non-randomized, and therefore was not intended to establish efficacy. The present study, LION (light vs ion therapy) extends this preliminary work as a fully powered, sham-controlled, participant-masked randomized controlled trial (NCT03968874), implemented as fully remote within the VA (target n = 120 complete). Randomization at 2:1 allocation ratio to: 1) active: MBLT (n = 80), and 2) sham: deactivated negative ion generator (n = 40); each with identical engagement parameters (60-min duration; within 2-hrs of waking; daily over 28-day duration). Participant masking via deception balanced expectancy assumptions across arms. Outcome measures were assessed following a 14-day baseline (pre-intervention), following 28-days of device engagement (post-intervention), and 28-days after the post-intervention assessment (follow-up). Primary outcomes were sleep measures, including continuous wrist-based actigraphy, self-report, and daily sleep dairy entries. Secondary/exploratory outcomes included cognition, mood, quality of life, circadian rhythm via dim light melatonin onset, and biofluid-based biomarkers. Participant drop out occurred in <10% of those enrolled, incomplete/missing data was present in <15% of key outcome variables, and overall fidelity adherence to the intervention was >85%, collectively establishing feasibility and acceptability for MBLT in Veterans with mTBI.

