**Modality**				
Remote (DocuSign consent)	39 (83%)	17 (77%)	20 (83%)	5 (45%)
In-Person (Physical copy consent)	8 (17%)	5 (23%)	4 (17%)	6 (55%)

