**Secondary Outcomes**				
Full questionnaire battery				
Pre-intervention	47 (100%)	22 (100%)	24 (100%)	11 (100%)
Post-intervention	43 (91%)	17 (77%)	20 (83%)	11 (100%)
Cognitive Assessment				
Pre-intervention	47 (100%)	22 (100%)	24 (100%)	11 (100%)
Post-intervention	45 (96%)	22 (100%)	23 (96%)	11 (100%)
DLMO				
Pre-intervention	40 (85%)	18 (82%)	21 (88%)	10 (91%)
Post-intervention	38 (81%)	19 (86%)	20 (83%)	11 (100%)
Biospecimen sample				
Pre-intervention	41 (87%)	19 (86%)	21 (88%)	9 (82%)
Post-intervention	40 (85%)	17 (77%)	20 (83%)	6 (55%)

Data are presented as mean ± standard deviation, or *n* (%). Pre-intervention assessments span a maximum of 14 days. Post-intervention assessments and device adherence spans a maximum of 28 days. DLMO, dim light melatonin onset.

With respect to participant retention, of the *n* = 140 participants who have provided informed consent, *n* = 24 have withdrawn or been terminated (Fig 3), and therefore *n* = 116 (83%) have been retained. At the time of this interim analysis, complete pre- and post-intervention data has been recorded in n = 104 participants and therefore the remaining n = 12 participants have been randomized/allocated and are currently ongoing.

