LION was originally conceived as, and initiated in, an in-person format typical for device-based randomized controlled trials. However, in response to the COVID-19 pandemic, this protocol was revised to enable its execution in a fully remote capacity. The remotely executed randomized clinical trial format is innovative in and of itself, but especially so considering this protocol was implemented within the VA. Indeed, success with this current design was the result of many years of preparation in establishing standard operating procedures, integrating VA regulatory, clinical, the Office of Information Technology, information security/privacy, biomedical, mailroom, and other services within the local and national VA system, as well as refinement of the protocol to reduce burden and enhance the participant experience. Specific aspects of this study protocol that were novel and logistically critical to its success include: 1) The implementation of an electronic digital signature service (DocuSign) for obtaining informed consent. This enabled research coordinators to screen, consent, and schedule future visits all on essentially the first point of contact, capitalizing on participant motivation and minimizing the potential for errors or PHI/PII exposure. 2) Establishing the logistical workflow for shipping equipment to and from participants’ place of residence in a manner that minimized participant burden and enabled transfer of biospecimens. 3) Effective utilization of video conferencing technology. 4) Establishing multiple recruitment modalities to effectively reach participants nationwide. 5) Leveraging the digital distribution (via TWILIO^™^ and REDCap) of key outcome measures (e.g., all participant questionnaire data and sleep diary entries), with automatic data entry directly into REDCap.

The present rate of participant retention (83%) either exceeds or is on par with other randomized clinical trials of similar scale and complexity, e.g., Lam et al: 81% [28]; Youngstedt et al: 68% [45]. Additionally, these metrics should also be viewed in the context of this protocol being in a fully remote format, which could potentially introduce additional sources of error and/or opportunity for drop out. Accordingly, the present interim analysis refutes this possibility, demonstrating strong protocol feasibility for the remote implementation of morning bright light therapy in Veterans.

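### The remote-feasibility conclusion rests on drop-out, adherence and completeness figures that the article's own Results do not support, and on a sample not separated by delivery mode

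*Protocol article*

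**What the plan says.** The overview in Materials and methods makes feasibility and acceptability of a fully remote trial the second aim, and the Results call evaluating them a central goal.

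- **Drop-out.** Abstract: "Participant drop out occurred in <10% of those enrolled". Results, after Table 3: "of the *n* = 140 participants who have provided informed consent, *n* = 24 have withdrawn or been terminated". The Results then report 116 (83%) retained, made up of 104 completers and 12 ongoing. The Discussion repeats 83% and compares it with 81% and 68% in two earlier trials.
- **Adherence.** Abstract: "overall fidelity adherence to the intervention was >85%, collectively establishing feasibility and acceptability for MBLT in Veterans with mTBI". The Results text gives an average of 83–93% across arms and defines full adherence as at least 20 of 28 days. The Discussion says 80–85% of the sample reported full compliance. Table 3 gives mean days of use.
- **Completeness.** The Table 3 footnote says: "Pre-intervention assessments span a maximum of 14 days". The Results text says more than 95% in both arms have ISI before and after the intervention.
- **Delivery mode.** One row of Table 1 is labelled "In-Person (Physical copy consent" and holds 23 of the 104 completers. On whether remote delivery adds error or drop-out, the Discussion says: "Accordingly, the present interim analysis refutes this possibility". It also concludes that remote delivery brought no meaningful rise in missing data.

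**The concern.** The article reports no efficacy results. These descriptive figures are its findings, and the second aim is judged on them. The headline numbers are more favourable than the counts reported further on. The statement about remote delivery is comparative, but no remote and in-person groups are compared.

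The practical stake is the planning of a later remote trial. As an illustration, take a target of 120 completers. A 10% loss calls for 120/0.90 = 133.3, so 134 consented participants. A 17.1% loss calls for 120/0.829, about 145, and an 18.8% loss calls for 120/0.8125, about 148. Recruiting 134 would yield about 109 to 111 completers instead of 120. The trial's efficacy estimand, sample size and analysis are not affected.

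**Working it through.** **1. Drop-out** (counts from the Results, after Table 3)

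- Retention reproduces: 116/140 = 82.9%, reported as 83%.
- The complement is 24/140 = 17.1%.
- The 12 ongoing participants have no known outcome. Without them the denominator is 140 − 12 = 128, drop-out is 24/128 = 18.8%, and completion is 104/128 = 81.3%. That is level with the 81% comparator, not above it.
- What would give under 10%? With all 140 in the denominator, at most 13 leavers (13/140 = 9.3%). With randomised participants only, at most 12 of the 24 leaving after randomisation: 12/(116 + 12) = 9.4%, whereas 13/129 = 10.1%. The text gives neither count.

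**2. Adherence** (Table 3, days of use out of 28)

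| Group | Calculation | Mean days | Share of 28 |
|---|---|---|---|
| MBLT, self-report | (47×22.8 + 22×24.6)/69 | 23.4 | 83.5% |
| Sham, self-report | (24×22.1 + 11×23.5)/35 | 22.5 | 80.5% |
| Both, self-report | weighted over 104 | 23.1 | 82.5% |
| MBLT, objective | 22.4 in both subgroups | 22.4 | 80.0% |

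Only one of the four self-report cells (88%, MBLT without TBI) is above 85%.

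The other possible metric is the share of participants reaching 20 days. The Discussion has 21, 5 and 1 MBLT participants non-adherent on one, two and three metrics, and 10 of the 21 failed the objective device metric. So between 10 and 10 + 5 + 1 = 16 of 69 failed it, and the share reaching the threshold lies between 53/69 = 76.8% and 59/69 = 85.5%. In sham, 9×1 + 4×2 = 17 failures spread about evenly over five metrics is about 3.4 of 35 per metric, or roughly 90% reaching the threshold.

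**3. Baseline SDs** (Table 3)

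For values between 0 and M with mean m in n people, the largest possible SD is √[m(M − m)·n/(n − 1)]. Here M = 14. The lowest mean that rounds to the printed value is used, which favours the table.

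| Cell | n | Printed | Largest possible SD |
|---|---|---|---|
| Diary, MBLT without TBI | 22 | 14.0 ± 3.4 | √(13.95×0.05×22/21) = 0.85 |
| Actigraphy, sham without TBI | 11 | 13.5 ± 5.4 | √(13.45×0.55×11/10) = 2.85 |
| Diary, sham mTBI | 24 | 13.0 ± 4.9 | √(12.95×1.05×24/23) = 3.77 |

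All other SDs in the day-count rows, including every device-adherence SD, are possible.

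**4. ISI completeness** (Table 3)

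All 104 have a pre-intervention ISI, so the post-intervention count limits the pairs. MBLT: (43 + 17)/69 = 87.0%. Sham: (21 + 10)/35 = 88.6%. Overall: 91/104 = 87.5%. None reaches 95%.

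**5. Delivery mode** (Table 1)

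In-Person: 8 + 5 + 4 + 6 = 23 of 104 (22.1%), with 13/69 (18.8%) in MBLT and 10/35 (28.6%) in sham. Remote: 39 + 17 + 20 + 5 = 81. Retention, adherence and completeness are not given separately for the two groups.

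**The case against.** Several points on the other side have force.

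- **Drop-out.** A reader might infer that the figure under 10% is simply false. The documents do not go that far. Randomisation followed consent and a two-week baseline, so some of the 24 may have left before allocation, and a post-randomisation rate could be under 10%. The CONSORT figure that might settle this is not shown. The 83% retention is also stated openly, twice. What stands is that the Abstract speaks of those enrolled and names no denominator, while the text's only count implies 17.1%.
- **Adherence.** A reader might infer that 82.5% directly contradicts a figure above 85%. It does not, because mean share of days and share of people reaching 20 days are different quantities, and the sham figures suggest about 90% on the second. What stands is that the metric is not named and that the three prose statements disagree. The Discussion's 80–85% with full compliance reads as the threshold share, yet it does not exceed 85%.
- **SDs.** The three cells are baseline diary and actigraphy. They bear on completeness only, not on drop-out or device adherence.
- **In-person share.** A reader might infer that 22% were run in person. The row is tied to consent format, and the consent section allows mailed paper forms with a phone call, so some of the 23 may have been remote. The in-person start is disclosed, and the Discussion does compare retention with outside trials. Neither supplies a comparison by delivery mode within this trial.
- **Efficacy models.** It may be tempting to ask for delivery mode as a covariate. That does not follow from a problem in reporting feasibility.

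**Conclusion.** The point holds as a reporting fault in the evidence for a stated secondary aim.

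- Drop-out is 17.1% of those consented, or 18.8% excluding those ongoing, against a headline under 10% that could hold only on a denominator or definition the text does not state.
- Adherence has three prose values that do not agree, on an unnamed metric, beside table means of 82.5% (self-report) and 80% (objective).
- Three SDs are arithmetically impossible if the 14-day maximum is right. Either those cells or the footnote must change.
- Paired ISI completeness is 87% and 89% by arm, not above 95%.
- The claim that remote delivery added no drop-out or missing data has no within-trial comparison behind it, however many of the 23 were truly in person.

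This rests on the counts in the text and Tables 1 and 3 being as printed, and on Fig 3 not being available. The documents do not show that remote delivery was infeasible, or that adherence missed the trial's own threshold.

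**What to change.** 1. Restate drop-out as 17–19% of those consented, or give the post-randomisation rate with its numerator and denominator. Say how ongoing participants are counted.
2. Name the adherence metric. Report the share reaching 20 of 28 days and the mean share of days separately, by arm, with self-report and objective measures apart. Make the Abstract, Results and Discussion agree.
3. Re-derive the three baseline cells in Table 3, or correct the 14-day maximum. Reconcile the ISI completeness statement with the table.
4. Classify participants by how the trial was actually delivered to them, not by consent form. Tabulate retention, adherence and completeness by that mode and base the remote conclusion on the remote participants. Drop the word *refutes* and the claim of no added missingness unless that table supports them.

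The cost is re-tabulation of data already held and somewhat less favourable headline figures. No change to the efficacy analysis is needed.

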## Introduction

Traumatic brain injury (TBI) can contribute to multiple short- and long-term negative neurologic sequelae, worsening functional outcomes and generating staggering economic burden [1]. One primary long-term complication associated with TBI (including mild TBI, mTBI) is sleep disturbance [2–4], with recent evidence demonstrating persistent post-concussive sleep-related impairment lasting several years [5] to >20 years post-injury [6–9]. The pathophysiology underlying persistent sleep disturbances after mTBI is unclear, but is potentially associated with damage to cortical pathways related to glutamate/GABA balance and/or orexin/hypocretin neurons, with subsequent effects on circadian-regulated systems such as melatonin and others [10–15]. Impaired sleep contributes to worse general health outcomes, including cognition, mood, and management of chronic pain, such that poor sleep exacerbates these outcomes which in turn further reduces sleep quality, creating a vicious cycle that is clinically very challenging to treat [16–21].

Clinically available interventions to treat sleep-wake disturbances, including in mTBI, often suffer from marginal efficacy, poor patient acceptability, and/or high patient/provider burden (e.g., medications, acupuncture, cognitive behavioral therapy for insomnia) [22–24]. Compounding this issue is the frequency of mTBI in Veterans and military service members, and associated high rates of mental health comorbidities, cognitive impairment, and chronic pain, all of which may limit the number of treatment options available or invite additional clinical considerations (e.g., pharmaceutical intervention, opioids, anti-depressants, or anxiolytics, to treat primary complaints, which often are accompanied by sleep impairing secondary effects including reducing slow-wave sleep, REM sleep or even melatonin production). Thus, alternative treatment approaches are needed in this population, particularly treatment options that are feasible, have high acceptability, are low burden, and have minimal side effects.

Light therapy, generally administered in the morning (i.e., morning bright light therapy; MBLT) is cost-effective, low-burden, home-based, and non-pharmacologic. Our recent single-arm, open-label clinical pilot study demonstrated preliminary feasibility and limited efficacy for MBLT to improve sleep, as measured both by self-report and objective actigraphy-based measures in Veterans with mTBI [25]. Much of the precedence for this pilot study stemmed from a large body of work associating mTBI with subsequent effects on sleep quality, mood and daytime alertness [26–39]. Additional rigorous studies have been executed comparing the effects of blue spectrum light with a placebo control amber light on sleep in individuals with mTBI, and found improvement in subjective daytime sleepiness, although objective measures of sleep via actigraphy were unchanged [40–42]. Two other recent studies examined light therapy on daytime fatigue in individuals with TBI (including severe TBI) [43,44]. Additionally, light therapy was also recently shown to improve post-traumatic stress disorder (PTSD) symptom severity in Veterans with PTSD, albeit without a change in self-reported or actigraphic metrics of sleep quality [45].

To our knowledge, the field of sleep medicine is without a fully powered, sham-controlled, masked, randomized controlled trial establishing feasibility, acceptability and efficacy of MBLT to improve sleep quality in Veterans with mTBI. Furthermore, to our knowledge, a fully remote randomized controlled trial device intervention protocol has not yet been successfully implemented in Veterans with mTBI–a challenging population not only due to significant participant disability/burden, but also due to the logistical and regulatory challenges of device management and electronic data capture behind the Veterans Affairs (VA) firewall. We sought to fill both gaps by implementing LION (Light vs Ion therapy), whose protocol is described herein. This trial proposed to acquire complete data in n = 120 Veterans allocated 2:1, active-intervention (MBLT, n = 80) versus sham-intervention (deactivated ion therapy, n = 40). MBLT delivered white light (10,000 lux at the eye), whereas the negative ion generator was fully deactivated, but modified to appear “on”, i.e., via installation of a small fan to generate a quiet, whirring sound, as well as a small LED status light. This sham-intervention was modeled from prior work by Lam et al., [28] in which bright light or sham-intervention therapy was compared to fluoxetine for the treatment of depression. Participants in both groups engaged with devices to the same extent (i.e., over 60 minutes within 2 hours after waking) throughout the 28-day intervention period, with the same degree of expectancy and study team interaction. The brand of the light box was chosen due to being commercially available, in use for decades (including within the VA), and previously validated for illuminance metrics and spectral power density [25]. Dose, timing, and duration were all established from prior work investigating the effect of MBLT for the treatment of insomnia, circadian entrainment, and seasonal affective disorder [46–48].

The proposed sham-controlled, participant-masked, randomized controlled trial was fully powered to establish efficacy for MBLT to improve sleep in Veterans with mTBI. Furthermore, this study—innovative in that it is being implemented as a fully remote protocol within the VA—also provides valuable feasibility and acceptability outcomes for the remote aspects of the study design for future iterations. This trial is currently ongoing with ~80% of participant enrollment completed. Therefore, this manuscript presents a detailed description of the clinical trial design, execution, interim feasibility/acceptability measures of the remote protocol, as well as the statistical analysis plan for future efficacy analyses once data collection is completed.

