## Materials and methods

### Overview and ethics

LION is a sham-controlled, participant-masked, randomized controlled trial (NCT03968874), investigating primarily, the efficacy of morning bright light therapy (MBLT) to improve sleep quality, cognitive function, and quality of life in Veterans with mTBI, and secondarily, the feasibility and acceptability of implementing a fully remote clinical trial within the VA. Participants were randomized and allocated 2:1 to active (MBLT) or sham (negative ion generator) study arms, with a target total sample size of n = 120 participants with complete pre- and post-intervention data (~80% of the data has been collected so far). Primary outcomes were changes between groups from baseline to post-intervention (28 days), and baseline to follow-up (56 days). All participants that expressed interest, screened eligible, and were enrolled in the study were processed according to the Standard Protocol Items and Recommendations for Interventional Trials (SPIRIT) guidelines (Fig 1). This project is sponsored by the Military Traumatic Brain Injury Initiative (MTBI^2^) and approved by a joint Institutional Review Board (IRB) at the VA Portland Health Care System (VAPORHCS; #4268 and #4002) and Oregon Health & Science University (OHSU; #19411), as well as the Department of Defense Office of Human Research Oversight (OHRO). All participants provided, or will provide, verbal and written informed consent prior to participation.

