**Fig 1 pone.0305305.g001:**
[figure not shown]
SPIRT outcomes across time. The Standard Protocol Items: Recommendations for Interventional Trials (SPIRIT) timeline for LION.

The total target sample size of n = 120 participants is based on a priori power analyses considering mean insomnia severity index score as the primary outcome (see below). Using a two-sided students t-test design comparing MBLT to sham (pre- to post-intervention), the minimal detectable clinically relevant between-group difference was set at 7% with a standard deviation of 12% within MBLT and 7.3% within sham groups. This approach achieves β = 0.15 with α = 0.05 (i.e., 85% power; 15% probability of incorrectly accepting the null hypothesis) [49,50].

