### Eligibility criteria

Eligibility criteria for enrollment included, over 18 years of age, able to provide informed consent and comply with the study protocol, no history of macular degeneration (contraindicated due to light therapy potentially exacerbating underlying pathology), no history of bipolar disorder (contraindicated due to light therapy potentially inciting a manic/depressive episode [31]), no shift work on third shift (e.g., 2300–0700 or equivalent) or any amount of days overnight, no current engagement in light therapy, and stable status on other pharmacological and/or behavioral sleep interventions.

This study originated in an in-person format with an exclusive focus on Veterans with mTBI, however protocol #4268 was amended to be conducted remotely, and expand recruitment to non-Veterans and to non-TBI participants, for the express purpose of increasing the diversity of this sample in terms of the number of women and individuals from racial/ethnic minority groups and increasing overall generalizability. See Table 1 for demographic parameters describing this current interim analysis.

History of mTBI was confirmed through a structured clinical interview using the Head Trauma Events Characteristics (HTEC; Table 2). The HTEC consists of a standard screening question followed by branching logic questions addressing injury type, location, intracranial injury/skull fracture, duration of loss of consciousness (LOC), and anterograde or retrograde post-traumatic amnesia (PTA), conferring a diagnosis of no, mild, moderate or severe TBI. Participants with an affirmative TBI outcome on the HTEC were excluded if their injury was moderate to severe and thus, the study only included participants with a history of mTBI. However, participants screening negative for TBI on the HTEC who met all other eligibility criteria, were also offered enrollment to promote generalizability throughout the wider VA.

**Table 2 pone.0305305.t002:** Current HTEC derived mTBI metrics.

	MBLT (*n* = 69)	Sham (*n* = 35)
	mTBI (n = 47)	mTBI (n = 24)
**Age at injury,** *years*	28.2 ± 17.4	29.6 ± 16.0
**mTBI recency,** *years*	26.2 ± 20.8	20.3 ± 15.0
**mTBI recency range**, *years*	2–67	1–52

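### The n = 120 and its 85% power are claimed for Veterans with mTBI but apply to an all-comer sample, of which Veterans with mTBI make up 62% so far

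*Protocol article*

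**What the plan says.** The Introduction ties the power claim to one population: "The proposed sham-controlled, participant-masked, randomized controlled trial was fully powered to establish efficacy for MBLT to improve sleep in Veterans with mTBI". It describes the sample in similar terms: "This trial proposed to acquire complete data in n = 120 Veterans allocated 2:1". The primary objective under Overview and ethics also concerns Veterans with mTBI, although the sample size there is worded more loosely, as a "target total sample size of n = 120 participants with complete pre- and post-intervention data".

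The power paragraph, printed after the Fig 1 caption, uses the Insomnia Severity Index (ISI) and a two-sided t-test: "the minimal detectable clinically relevant between-group difference was set at 7% with a standard deviation of 12% within MBLT and 7.3% within sham groups". It concludes: "This approach achieves β = 0.15 with α = 0.05 (i.e., 85% power".

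Eligibility criteria then reports that the protocol was amended to "expand recruitment to non-Veterans and to non-TBI participants", with diversity and generalisability as the reason. Results and Discussion count all 104 completers against the 120. Statistical analyses includes everyone randomised under intention to treat and fits treatment, time and their interaction. The optional covariates named there include neither TBI status nor Veteran status, and no mTBI analysis set is described.

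**The concern.** The claimed population is Veterans with mTBI. The population counted and analysed is adults with or without mTBI, Veteran or not. The amendment changed the second and left the objective, the sample-size statement and the power claim unchanged.

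This affects what the trial can conclude. A positive pooled result would be reported for a group forming 62% of the sample, without a described estimate for that group. A null pooled result could not be read as evidence against benefit in that group, because the document neither states nor tests whether the effect is the same with and without TBI. A reader would also take 85% power at n = 120 as applying to Veterans with mTBI, when only about 74 of them are expected.

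**Working it through.** **Counts (Table 1).**
- mTBI: 47 + 24 = 71 of 104 (68%). No TBI: 22 + 11 = 33.
- Veterans with mTBI: 46 + 18 = 64 of 104 (62%).
- Non-Veterans: 1 + 8 + 6 + 1 = 16.

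**Projection to 80 MBLT and 40 sham at the same shares.**
- mTBI: 80 × 47/69 = 54.5 and 40 × 24/35 = 27.4, about 82 in total (54/27 used below).
- Veterans with mTBI: 80 × 46/69 = 53.3 and 40 × 18/35 = 20.6, about 74 in total (53/21 used below).

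**Reproducing the stated 85%.** Power comes from the noncentral t distribution with noncentrality difference/SE, two-sided alpha 0.05, difference 7.
- SD 12 in both arms: SE = 12 × √(1/80 + 1/40) = 2.324; noncentrality 7/2.324 = 3.01; power 0.848. This matches.
- SDs 12 and 7.3, unequal variances (Welch): SE = √(144/80 + 53.29/40) = 1.770; noncentrality 3.96; power 0.975. This does not match.

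So 85% at 80/40 follows from 12% in both arms, although the text states two SDs. Both bases are carried forward.

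**Power for the named population, 7% difference.**

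| Group | n (MBLT/sham) | SE, SD 12 both | Power | SE, SDs 12/7.3 | Power (Welch) |
|---|---|---|---|---|---|
| All-comers | 80/40 | 2.324 | 85% | 1.770 | 97.5% |
| mTBI | 54/27 | 2.828 | 69% | 2.154 | 89% |
| Veterans with mTBI | 53/21 | 3.094 | 61% | 2.292 | 85% |

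**All-comer power if the effect differs by TBI status.** The documents give no effect for non-TBI participants, so three assumed values are shown. With 7% in mTBI and a fraction f of it in the others, the pooled effect is 7 × (71 + 33f)/104.

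| f | Pooled effect | Power, SD 12 both | Power, SDs 12/7.3 (Welch) |
|---|---|---|---|
| 0 | 4.78% | 53% | 76% |
| 0.5 | 5.89% | 71% | 91% |
| 1 | 7.00% | 85% | 97.5% |

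**Primary-outcome data so far (Table 3).** Post-intervention ISI exists for 43 + 21 = 64 of the 71 mTBI completers, Veterans and non-Veterans together. The projections above assume the outcome is present for every completer, so they are somewhat generous.

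**The case against.** **The widening is disclosed and reasoned.** The amendment and its purpose are stated openly. The Introduction's wording about what was proposed can be read as the original design, and the Methods speak of 120 participants without qualification. That is fair, but the primary objective in the Methods still names Veterans with mTBI, so the passages remain unreconciled.

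**A separate analysis plan may add the TBI term.** Covariates are optional and the list is open-ended, so the absence of TBI status is not a defect in itself. The mismatch between the population claimed and the population counted does not depend on it.

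**The power claim may survive.** A reader might infer that the trial is underpowered for Veterans with mTBI. The document does not settle this: with both stated SDs the projected group still reaches 85%, and only with 12% in both arms does it fall to 61%.

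**Dilution is not established.** The dose and timing were drawn from work on insomnia, circadian entrainment and seasonal affective disorder, so no effect in people without TBI is not an obvious default. It is one end of the range shown.

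**Veteran status by arm.** Within mTBI, 46/47 on MBLT and 18/24 on sham are Veterans (Fisher p = 0.005). A reader might infer that the pooled comparison is confounded. Across all completers the split is 60/69 (87%) against 28/35 (80%), p = 0.40, so the table does not support that. The imbalance is a reason to adjust the within-mTBI estimate.

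**An mTBI-only primary analysis is not the only remedy.** It would still include 7 non-Veterans among 71, and it would change the primary population late in a trial whose investigators know that every ion generator is inactive. This objection stands.

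**Conclusion.** The point holds as a mismatch of populations. The objective, the sample size and the power claim are stated for Veterans with mTBI, while the 120 is being filled, and will be analysed, as an all-comer sample. Veterans with mTBI are 64 of 104 now and about 74 of 120 if the shares persist.

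The 85% therefore describes the all-comer comparison. For the named population, power for a 7% difference is about 61% on the SD basis that gives 85% at 80/40, or 85% with the two stated SDs. For all mTBI participants the figures are 69% and 89%. These rest on constant enrolment shares, the plan's own difference and SDs, and a complete primary outcome.

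The documents do not support a flat statement that the trial is underpowered, that the pooled effect is diluted, or that pooling is biased by Veteran status.

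**What to change.** Before efficacy analysis, reconcile the Introduction, the objective and the power paragraph with the amended eligibility criteria:

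1. Name the primary analysis population, and restate n and power for it with the SD basis used.
2. If all randomised participants remain primary, word the objective and conclusion for adults with or without mTBI.
3. In that case, also prespecify the randomised comparison within mTBI participants and a treatment-by-TBI interaction, with baseline TBI and Veteran status as covariates.

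The cost is wording and a few lines of analysis plan. TBI and Veteran status are already recorded, and Results says that formal analyses of the outcomes have not yet been explored.

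There are two drawbacks. The stated power for Veterans with mTBI will be less favourable than the present claim. The interaction test will also be weak. With about 54/27 mTBI and 26/13 non-TBI participants, its SE is √(144/54 + 144/27 + 144/26 + 144/13) = 4.96 with SD 12 in both arms, or 3.78 with SDs 12 and 7.3. Even if the whole 7% effect were absent without TBI, power would be about 29% or 46% (normal approximation). The interaction should therefore be reported as an estimate with its interval, and a non-significant result should not be read as evidence of equal effect.
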